## Introduction

Patellofemoral pain (PFP) is characterized by the presence of pain around or behind the patella, exacerbated by activities that increase patellofemoral joint loading [1]. PFP is prevalent in young adults and adolescents (22.7% and 28.9%, respectively), with women being twice as likely to develop PFP than men [2]. People with PFP typically report reduced levels of physical activity [3], functional capacity [4, 5], and quality of life [6]. Evidence also indicates that symptoms can be long-lasting, with 50 to 91% of people with PFP experiencing persistent pain up to 18 years after the initial diagnosis [7].

According to the International Association for the Study of Pain (IASP) [8], the concept of pain encompasses more than just physical-chemical aspects of nociception. Sociocultural, emotional, and cognitive factors can also contribute to the worsening of pain and dysfunction [9–13]. This seems to apply to people with PFP as they present with altered psychological factors such as anxiety, depression, pain catastrophizing, and kinesiophobia [11]. Moderate correlations between psychological factors with pain and disability have also been reported in people with PFP [14].

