Internet-based interventions have been recently promoted due to their potential to overcome geographical barriers, increase access to health services, and provide alternative means to continue treating patients whenever face-to-face encounters are precluded [32]. There is evidence supporting the use of internet-based interventions for the treatment of several conditions [33, 34] as they may provide similar improvements in pain and function compared to face-to-face treatments [35, 36]. Furthermore, internet-based interventions may allow patients to assume a more active role in their rehabilitation, encouraging strategies as self-management and self-efficacy [33]. Online MBI has also been shown to be feasible and effective in reducing psychological factors such as stress, anxiety and depression [37]. However, few studies have investigated the effects of internet-based interventions for PFP, especially including components targeting psychological factors such as MBI.

The aims of this randomized clinical trial are:

(i)to investigate the immediate (8-week) and long-term (12-month) effects of adding the MBI program to an 8-week online intervention comprised of exercise therapy and patient education on self-reported recovery, pain, function, and psychological factors in people with PFP;(ii)to investigate whether changes in psychological factors mediate changes in pain and function.

We hypothesize that people in the Mindfulness group will experience greater decreases in pain, as well as higher improvements in function at 8 weeks and 12 months. We also hypothesize that psychological factors such as kinesiophobia and pain catastrophizing will mediate changes in pain and function.

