### Statistical analysis

Statistical analysis will be performed by the blinded assessor using SPSS software (IBM version 23, SPSS Inc., Chicago, Il). Descriptive statistics will be computed for all variables (e.g. mean, standard deviation). Data will be tested for normal distribution by the Shapiro-Wilk test. Chi-square tests will be performed to compare self-reported recovery (successful x unsuccessful) between groups. For continuous data, the effects of group, time and their interaction will be assessed with linear mixed models. Intraclass Correlation Coefficients will be used to determine the amount of variance explained by random effects [69]. The Bonferroni-adjusted *post hoc* test will be performed for multiple pairwise comparisons where appropriate. Effect sizes (95% CI) (Cohen’s d) will also be calculated and interpreted as follows: Cohen’s = 0.2 ‘small effect’; = 0.5 ‘moderate effect’; = 0.8 ‘large effect’ and = 1.3 ‘very large effect’ [70]. Intent-to-treat analyses will be performed for all outcomes. Multiple imputation will be used to account for missing data if the proportion of missing data is > 5% [71]. For all tests, an α level of 0.05 two-tailed will be adopted to indicate statistical significance.

The mediation effects will be assessed following the 3-variable framework described by MacKinnon et al. [72]. In this model, the intervention condition is assumed to have both direct and indirect paths to the changes in clinical outcomes. The indirect path passes through the potential mediators (anxiety, depression, kinesiophobia, pain catastrophizing and pain self-efficacy). Three multiple regressions will be performed: [1] to test the association between the predictor (i.e., interventions) and the outcomes (i.e., pain and function); [2] to test the association between the predictor and the potential mediators and [3] to test the association between the potential mediators and the outcomes after controlling for the predictor. Then, it will be observed whether the association of the predictor with the outcome after controlling for potential mediators will be smaller than observed in the first regression.

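### The mediation regressions do not carry the changes of aim (ii) through to the mediators and adjust the mediator-outcome path for arm only, leaving the collected baseline scores as an unadjusted common cause

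*Protocol article*

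**What the plan says.** The second aim in the Introduction is "to investigate whether changes in psychological factors mediate changes in pain and function". It refers to change on both the mediator side and the outcome side.

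The mediation paragraph under Statistical analysis refers to change once, for the outcome: "the intervention condition is assumed to have both direct and indirect paths to the changes in clinical outcomes". The mediators are then listed by scale, with no change, time point or baseline attached: "The indirect path passes through the potential mediators (anxiety, depression, kinesiophobia, pain catastrophizing and pain self-efficacy".

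Three regressions follow:

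- Regression 1: "to test the association between the predictor (i.e., interventions) and the outcomes (i.e., pain and function".
- Regression 2: "to test the association between the predictor and the potential mediators".
- Regression 3: "to test the association between the potential mediators and the outcomes after controlling for the predictor".

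Mediation is then judged by whether "the association of the predictor with the outcome after controlling for potential mediators will be smaller than observed in the first regression".

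The Outcome measures section has every scale assessed at baseline, at 8 weeks and 12 months after the intervention ends. No baseline score appears in any of the three regressions. The Introduction also states: "Moderate correlations between psychological factors with pain and disability have also been reported in people with PFP".

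**The concern.** Randomisation makes the arms comparable, so it protects the arm-to-mediator and arm-to-outcome comparisons. It does not protect the mediator-to-outcome comparison in regression 3, because nobody is randomised to a level of catastrophizing or kinesiophobia. Participants who start with worse psychological scores also tend to start with more pain, and both tendencies persist to follow-up. Baseline severity is therefore a common cause of mediator and outcome. It is measured, and the regressions as described leave it out.

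The wording also leaves open whether mediator and outcome are follow-up scores, change scores or one of each. These choices do not give the same answer, and some err in opposite directions. At stake is the answer to one of the trial's two stated aims.

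**Working it through.** **Inputs.** From the article: 62 participants, 1:1 allocation, two-sided 0.05, arm as the stated control in regression 3, and a moderate existing correlation (no figure given). Assumed, because the article gives no values: baseline mediator-outcome correlation r = 0.3 to 0.5, retest correlation ρ = 0.5 to 0.7, and a 0.5 SD arm effect on both mediator and outcome. The article gives no figure of its own to reproduce on this point.

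**Model with no mediator effect conditional on baseline.** Baselines M0 and Y0 have variance 1 and correlation r. Follow-up scores are M1 = ρM0 − 0.5·arm + noise and Y1 = ρY0 − 0.5·arm + independent noise, with noise variance 1 − ρ². The within-arm variance at follow-up is then also 1.

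**Within-arm correlation that regression 3 picks up:**

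- Follow-up on follow-up: ρ²r. From 0.5² × 0.3 = 0.075 to 0.7² × 0.5 = 0.245.
- Change on change: r(1 − ρ)/2. From 0.3 × 0.3/2 = 0.045 to 0.5 × 0.5/2 = 0.125.
- Outcome change on follow-up mediator: −ρr√((1 − ρ)/2). From −0.5 × 0.3 × 0.5 = −0.075 to −0.7 × 0.5 × √0.15 = −0.136.
- Follow-up on follow-up, both baselines in the model: 0.

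As a check on the largest value, regression 3 has 62 − 3 = 59 residual degrees of freedom. The non-centrality is 0.245 × √59/√(1 − 0.245²) = 0.245 × 7.68/0.970 = 1.94, against a critical t of about 2.00. Slightly under half of trials should be significant, which agrees with the simulation.

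**Simulated results over the assumed range, n = 62:**

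| Reading | Mediator term p < 0.05 | Arm coefficient smaller |
|---|---|---|
| Follow-up scores, arm only | about 7-49% | about 70-92% |
| Change scores, arm only | about 6-17% | about 63-79% |
| Outcome change, follow-up mediator, arm only | about 8-19% | about 16-29% |
| Follow-up scores, both baselines added | about 5% | about 50% |

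With no mediation, a rule that asks only whether a coefficient is smaller should be met about half the time by chance, as in the last row.

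**Why the direction differs.** With the same participants and covariates in both models, the arm coefficient moves by exactly a·b, where a is the arm effect on the mediator and b the mediator coefficient.

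- Follow-up scores at r = 0.5, ρ = 0.7: a·b = −0.5 × 0.245 = −0.12. This has the same sign as the arm effect of −0.5, so that effect appears partly explained.
- Outcome change on follow-up mediator, same setting: b = −ρ(1 − ρ)r = −0.7 × 0.3 × 0.5 = −0.105, so a·b = +0.05. The arm coefficient grows and mediation is masked.
- If arm does not move the mediator, a = 0 and the spurious indirect effect averages zero whatever r is.

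**Second set of assumptions.** These used 52 analysed participants, a 0.78 SD arm effect on the outcome (4.2/5.4, from the sample size section) and r of 0.3 or 0.5. Follow-up scores gave a significant mediator term in 7.5-43% of runs, change scores in 6-14% and the baseline-adjusted model in 4.5-5.6%. With follow-up scores and an arm effect on the mediator of 0.5-0.78 SD, 5-25% of the arm effect looked mediated when none was.

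**The case against.** **The text is ambiguous, not plainly at odds with the aim.** A reader might infer that the regressions use raw follow-up scores and so contradict aim (ii). The documents do not support that. The paragraph opens with paths to changes in clinical outcomes, and the later mention of pain and function may only name which outcomes enter. This stands: the upper rates of 34-49% belong to one reading. Even so, none of the three arm-only readings holds the nominal 5% across the assumed range.

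**The simulated change scores are related.** Their within-arm correlation is r(1 − ρ)/2, or 0.045 to 0.125. The 6-17% for change scores is therefore false only if change means change conditional on baseline. This stands, and it is why that meaning should be stated.

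**A significant regression 3 is not a finding of mediation.** A reader might take the 49% as a rate of false mediation claims. It is not, because the arm-mediator regression and the coefficient comparison also count. When both the arm-mediator and mediator-outcome terms must be significant, the rates at n = 62 are about 3-24% (follow-up scores), 4-7% (change scores) and 2-4% (baseline-adjusted). Baseline correlation alone is also not enough, since arm must move the mediator. That condition is what the trial hypothesises.

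**Covariates may be left to a statistical analysis plan.** A plan not shown could add baseline terms, and describing all three steps as multiple regressions does not exclude them. But the article writes out each regression and names the control for the third. The point addresses that stated choice.

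**The inputs are assumed.** This is true. The size of the bias is not established by the documents, only its presence under any positive baseline correlation that persists to follow-up.

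**Conclusion.** The point holds in a limited form. The mediation paragraph does not carry change through from aim (ii) to the mediators and the regressions. It names arm as the only control on the one path that randomisation does not protect, although the relevant baseline scores are collected.

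Under the stated assumptions the mediator term is significant too often on each reading the text allows, and adding both baselines brings it back to about 5%. The coefficient comparison leans towards mediation on follow-up or change scores, and against it when outcome change is paired with a follow-up mediator. The same data could thus support or weaken aim (ii) through a choice the article does not make. The size depends on the assumed correlations and arm effects.

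The primary outcomes and the between-group comparisons are not affected. The change should be made before the mediation analysis is run.

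**What to change.** In the mediation paragraph of Statistical analysis:

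1. Define mediator and outcome as follow-up scores at a named time point, and state that change in aim (ii) means change conditional on baseline.
2. Add the baseline outcome to regression 1, the baseline mediator to regression 2, and both to regression 3.
3. When comparing the arm coefficient with and without the mediator, fit both models with the same baseline covariates, so that the difference reflects the mediator alone.

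The cost is one or two degrees of freedom per model, out of about 60, and a few sentences of text. No new data are needed. Baseline adjustment removes only the confounding already measured. Unmeasured common causes of mediator and outcome remain and should be acknowledged when the mediation results are interpreted.

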## Discussion

PFP is a common and often recalcitrant knee disorder, with symptoms persisting for many years [7]. Exercise therapy and patient education are considered the “best management” options for this population [15, 16]. However, unsatisfactory long-term prognosis remains an issue [17]. It is known that people with PFP present with altered psychological factors [11], which should be considered during the evaluation and treatment of people with PFP [19]. Recent studies suggest that MBI induces functional and structural brain modifications [24, 25]. As part of a rehabilitation program, MBI can help the patients to recognize and accept their condition, promoting a more effective focus on rehabilitation and facilitating pain relief [28, 73]. Therefore, adding a MBI program to the current best treatment for PFP may improve psychological outcomes, providing a better response to treatment at short and long-term. However, this hypothesis needs further investigation. The proposed trial will address this knowledge gap by evaluating the effects of adding an 8-week online MBI program to an online program of exercise therapy and patient education on self-reported recovery, pain, function and psychological factors and in people with PFP. If our hypotheses are confirmed, our findings will contribute to the discussion of a new perspective of treatment modality for people with PFP.

### Limitations

This study investigates the additional effect of an online treatment based on mindfulness program to exercise therapy and patient education for people with PFP. Although exercise therapy and patient education are considered the cornerstones of PFP management [16, 19], the additional effect of the mindfulness intervention to all physical interventions of PFP is not investigated in the present study. Future studies in this area are warranted.

## Data Availability

Not applicable.

## Abbreviations

AKPS: Anterior Knee Pain Scale
CPSS: Chronic Pain Self-Efficacy Scale
GROC: global rating of change scale
HADS: Hospital Anxiety and Depression Scale
IASP: International Association for the Study of Pain
MBHP: Mindfulness-Based Health Promotion
MBI: Mindfulness-based interventions
PCS: Pain Catastrophizing Scale
PFP: Patellofemoral pain
ReBEC: *Registro Brasileiro de Ensaios Clínicos*
SPIRIT: Standard Protocol Items:Recommendations for Interventional Trials
VAS: visual analogue scale.
